##### Safety assessments

2.3.7.3

The direct investigator will record all adverse events related to bowel preparation regime and colonoscopy such as nausea, vomiting, bloating, abdominal pain, and electrolyte imbalance into the case report form (CRF). That is to say, when an adverse event occurs, the investigator will record the symptoms and signs of the adverse reaction, the duration (start and end date), severity, course, outcome, significance, and any action taken in relation to the adverse event. It is noted that any symptom that existed before the start of the bowel preparation will not be recorded as adverse events.

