## Abstract

Colonoscopy has been regarded as an important method of early diagnosing and treating gastrointestinal lesions; however adequate bowel preparation is critical one of many factors needed for successful colonoscopy. Although several modified or novel regimes have been developed, desired quality of bowel preparation has not yet been generated. Scattered evidences revealed that castor oil may have potential of effectively cleansing colon. It is noted that, however, prospective trial of exploring the value of castor oil in preparing bowel before colonoscopy is lacking. The aims of this study are to test the hypotheses that low dose castor oil (30 mL) may enhance potential of polyethylene glycol (PEG) and combination of low castor oil and ascorbic acid may halve the volume of PEG.

This is a randomized, double-blind (endoscopist and assessor), single center trial with three-arm design. We will randomly assign 282 adult patients (≥18 years but < 75 years), who are scheduled to undergo colonoscopy, to receive either 3 L PEG alone, 2 L PEG plus 30 mL castor oil or combination of 1 L PEG, 30 mL castor oil and 5 g ascorbic acid. The bowel preparation quality based on Boston Bowel Preparation Scale (BBPS) is the primary outcome. The secondary outcomes include the first defecation time, total number of defecation, time of cecal intubation, detection rate of polyp and adenoma, willing to repeat the same regime, tolerance to regime, and adverse events.

The study protocol has been approved by the Clinical Research Ethics Committees of Chongqing University Cancer Hospital & Chongqing Cancer Institute & Chongqing Cancer Hospital & Chongqing Cancer Center (2017[107]). The results from this trial will be submitted for publication in peer-reviewed journals, and will be presented at national and international conferences.

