Castor oil is a safe, effective, and cheap laxative with highly efficacious for colon cleans,^[12]^ which has been widely used as the laxative in many settings such as intravenous urography.^[13–15]^ Apisarnthanarak et al^[12]^ found that castor oil and sodium phosphate (NaP) obtained similar patients’ satisfaction and efficacy of colon cleans for barium enema. The trial performed by Yang et al^[15]^ observed no difference in laxative efficacy between castor oil and bisacodyl for intravenous urography. It must be noted that, moreover, combination of bisacodyl and PEG^[16]^ and combination of NaP^[17]^ obtained promising bowel preparation efficacy, decreased the required volume of liquid, and improved the compliance with the recommended regime when compared to standard PEG regime. Moreover, the potential of 2 L PEG plus ascorbic acid is equal to that of 3 L PEG,^[18]^ and which is better than that of 2 L PEG plus NaP.^[19]^ And thus, we speculate that combination of 2 L PEG and castor oil may have similar potential with 2 L PEG plus bisacodyl or NaP for colon cleanses, and which is not inferior to the potential of 3 L PEG. More importantly, 2 trials^[20,21]^ found that combination of 1 L PEG, bisacodyl, and ascorbic acid improved the patient's tolerability and did not compromise bowel preparation efficacy compared with combination of 2 L PEG and ascorbic acid. So, we also speculate that combination of castor oil and ascorbic acid may have the potential of halving the required volume of PEG.

Published evidences^[22–24]^ suggested that large dose castor oil (50 or 60 mL) may be more likely to cause some adverse effects such as abdominal cramping, vomiting, nausea, abdominal fullness, fainting, and insomnia. However, some trial^[12]^ found that the incidence of adverse events in low dose castor oil (30 mL) is lower than that of NaP. So, we hypothesize that 30 mL castor oil may enhance potential of PEG, and combination of 30 mL castor oil and ascorbic acid (5 g)^[25]^ may halve the required volume volume of PEG.

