#### Recruitment, randomization, and blinding

2.3.4

The day before colonoscopy, investigators who have been trained for the study and are authorized by the principal investigator will assess candidates according to the inclusion and exclusion criteria. After eligible patients were identified, the written informed consents will be obtained from the eligible patients, their next of kin or legal representatives. At the phase, the investigators will also collect demographic and clinical characteristics data of all eligible patients, which includes sex, age, body weight, body mass index, reasons for colonoscopy, previous colonoscopy history, and comorbidity such as hypertension, diabetes mellitus, and cardiovascular disease.

All recruited patients will be randomly assigned to receive one of the 3 preparation regimes including 3 L PEG, combination of 2 L PEG and 30 mL castor oil, and combination of 1 L PEG, 30 mL castor oil, and 5 g ascorbic acid. We will generate the random sequence by using SPSS 17.0 software, and the random sequence will be sealed in opaque envelope. An independent research nurse will be designated to random all patients into 3 different groups according to the random sequence.

In order to eliminate the risk of bias as much as possible, the endoscopists will be blinded except the research nurse who conducted the randomization procedure during examine period. Moreover, we will also blind the biostatistician.

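### As worded, the protocol records only adverse events attributed to the preparation or colonoscopy, so a judgement on cause comes before data capture

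*Protocol article*

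**What the plan says.** Section 2.3.7.3 gives the capture rule: "The direct investigator will record all adverse events related to bowel preparation regime and colonoscopy". It names gut symptoms and electrolyte disturbance as examples. The next sentence opens as an explanation of that rule: "when an adverse event occurs, the investigator will record the symptoms and signs of the adverse reaction". It goes on to list the dates of the event and "severity, course, outcome, significance, and any action taken in relation to the adverse event". Relatedness is not on the list. The section then states one further exclusion, which concerns timing: "any symptom that existed before the start of the bowel preparation will not be recorded as adverse events".

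The Abstract ends its list of secondary outcomes with "willing to repeat the same regime, tolerance to regime, and adverse events" and attaches no condition about cause. Section 2.3.7.2 (Secondary outcomes) does not name adverse events, so section 2.3.7.3 is the only place where their collection is defined.

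On blinding, section 2.3.4 says "the endoscopists will be blinded except the research nurse who conducted the randomization procedure during examine period" and adds the biostatistician. The Abstract and section 2.2 describe the trial as double-blind for endoscopist and assessor.

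**The concern.** Randomisation supports a comparison of everything that happens to patients after assignment. It gives no such support to a comparison of events already selected by an opinion on their cause. If relatedness is the entry condition, the safety data are narrower than the outcome in the Abstract, and no later analysis can widen them because the excluded events were never written down.

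This matters more than usual here. The Abstract says that prospective trial evidence on castor oil before colonoscopy is lacking, so an investigator has little basis for deciding beforehand which symptoms the regimen could cause. The schedule in section 2.3.5 also supplies rival explanations for a symptom: an overnight fast, drinking in the small hours, and propofol sedation.

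**Working it through.** **Text check.** The point does not depend on any sample size, power or event count in the protocol, so there is no figure to reproduce. The question is whether the recording rule is limited by cause, and whether anything elsewhere lifts the limit.

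1. The first sentence of section 2.3.7.3 restricts the events by their relation to the regimen and the colonoscopy.
2. The second sentence explains the first rather than extending it. It begins with an adverse event but records the signs of the adverse *reaction*, a term that presumes a cause.
3. The listed items contain no causality item. Relatedness therefore acts as a filter and is not data that can be reviewed later.
4. No other section provides for recording events regardless of cause.
5. Three sources carry no stated relatedness condition: electrolytes before and after preparation (2.3.7.4), treatment and drugs given (2.3.6), and tolerance on a 4-point scale (2.3.7.2). What remains exposed is mainly untreated clinical symptoms.

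**Illustration 1: an unexpected event missed altogether.** The assumptions are 282/3 = 94 patients per arm (the allocation ratio is not stated), a true event rate r, and a share s of events judged unrelated and not recorded. Neither r nor s comes from the protocol.

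P(arm records none) = (1 − r(1 − s))^94

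For r = 2% and s = 50%: (1 − 0.02 × 0.5)^94 = 0.99^94 = 0.389.

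| True rate r | s = 0 | s = 50% | s = 80% |
|---|---|---|---|
| 1% | 39% | 62% | 83% |
| 2% | 15% | 39% | 69% |
| 3% | 6% | 24% | 57% |

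This calculation needs no difference in filtering between arms.

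**Illustration 2: a common event.** Recorded rate = true rate × share judged related. All rates and shares are assumed.

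- Same share in both arms, true rates 20% and 30% (a 10-point difference). At a 60% share the record shows 0.20 × 0.60 = 12% and 0.30 × 0.60 = 18%, a 6-point difference. At a 90% share it shows 18% and 27%, a 9-point difference. The difference shrinks but keeps its direction.
- Different shares, true rate 30% in both arms. At 60% and 90% the record shows 0.30 × 0.60 = 18% and 0.30 × 0.90 = 27%, a false 9-point difference.
- Different shares the other way, true rates 20% and 30%. At 90% and 60% the record shows 0.20 × 0.90 = 18% and 0.30 × 0.60 = 18%, so the difference vanishes.

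The last two cases only show what arm-dependent filtering could do. The shares in the final case were picked so that the products cancel exactly.

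**The case against.** **The filter is partly inferred.** The protocol does not say that *only* related events are recorded. Its second sentence can be read as covering any adverse event, and the one explicit exclusion is about timing. A condensed article may also leave the form's fields to a fuller document. This stands as a reason to call the wording ambiguous. It does not remove the point, because the article itself states the capture rule, and the explanatory opening and the term *reaction* favour the narrower reading.

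**Little may fall outside the rule.** The symptoms named as examples are expected effects of a purgative and are unlikely to be called unrelated. An event put down to the early-morning intake could count as related to the regimen, and one put down to sedation as related to the colonoscopy. The schedule runs only from the evening before to a morning procedure. All of this limits the likely loss, but none of it settles how a borderline symptom is handled.

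**A reader might infer that the loss favours one arm.** Patients are not stated to be blinded, the regimens differ visibly, and patients could reveal their regimen when reporting symptoms. But the protocol claims endoscopist and assessor blinding, and it does not say whether the direct investigator who records events is blinded. Section 2.3.6 has direct investigators deciding whether the colonoscopy goes on, which suggests an endoscopist, while section 2.3.7.2 names the two roles separately. The fast and the intake times are common to all three arms. Arm-dependent filtering is possible but not established.

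**A reader might infer that known effects of the trial's castor oil dose would be dropped.** The Introduction does list "abdominal cramping, vomiting, nausea, abdominal fullness, fainting, and insomnia", but it ties them to 50 or 60 mL and contrasts that with 30 mL, where one cited trial found fewer adverse events than with sodium phosphate. The list is not evidence of what 30 mL causes.

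**Conclusion.** The point holds as a fault in the wording of the recording rule. Followed as written, section 2.3.7.3 puts a judgement on cause ahead of data capture and does not list that judgement as data, while the Abstract names adverse events as an outcome without the limit. Untreated clinical symptoms judged unrelated would be lost to analysis. It would be too strong to say that safety data in general are lost, because electrolytes, treatments given and tolerance bypass the filter.

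The size is unknown. The figures above rest on assumed event rates, assumed shares filtered out and equal arms of 94. They show that filtering can hide a rare event or shrink a difference, not that it will. The direction of any bias between arms is uncertain. The primary outcome is unaffected. This is a low-cost improvement to a secondary safety outcome, and it has to be made before data collection to be of use.

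**What to change.** Reword the first sentence of section 2.3.7.3 along these lines: *every untoward event from the first dose of the assigned regimen onward is recorded, whatever its suspected cause.* Add relatedness (regimen; colonoscopy or sedation; neither) as a separate field on the case report form, completed after the event has been entered. State that arms are compared first on all recorded events and second on those judged related.

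This takes one sentence, one field and a line in the analysis section, with no new visits or staff. The downside is a few more unrelated events to record.

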#### Inclusion criteria

2.3.1

Participants will be enrolled if the following criteria were met: age above 18 and under 75 years; adult outpatients who will be scheduled to undergo morning colonoscopy regardless of sex; did not participate in other clinical trials which also aimed at investigating bowel preparation efficacy; and agree to participate, and give signed written informed consents.

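### The adverse event rule makes no exception for worsening of a pre-existing symptom, so symptom-specific event rates are under-counted in all three arms

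*Protocol article*

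**What the plan says.** Section 2.3.7.3 (Safety assessments) has investigators enter adverse events related to the regimen and to the colonoscopy, naming "nausea, vomiting, bloating, abdominal pain, and electrolyte imbalance into the case report form". Once an adverse event has occurred, they also record "the duration (start and end date), severity, course, outcome, significance, and any action taken in relation to the adverse event". The section closes with an exclusion: "any symptom that existed before the start of the bowel preparation will not be recorded as adverse events". Worsening is not mentioned.

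Section 2.3.4 (Recruitment, randomization, and blinding) lists what is collected at the visit on the day before colonoscopy: "sex, age, body weight, body mass index, reasons for colonoscopy, previous colonoscopy history, and comorbidity such as hypertension, diabetes mellitus, and cardiovascular disease". A graded record of current symptoms is not on that list.

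The abstract names adverse events as a secondary outcome. Section 2.3.1 admits "adult outpatients who will be scheduled to undergo morning colonoscopy regardless of sex". Section 2.3.2 excludes, among others, patients with chronic constipation and known motility disorders, but not patients with current pain, nausea or bloating.

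**The concern.** The exclusion turns on whether a symptom existed beforehand, not on whether it changed. A mild complaint that becomes severe after the preparation is treated in the same way as one that stays mild. Severity is captured only for something that already counts as an adverse event, so the worsening leaves no trace in the symptom data. No graded baseline is listed against which it could be reconstructed. A later analysis plan cannot recover what was never entered on the form, so the rule has to be changed before data are collected.

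At stake is the safety comparison. The Introduction argues for 30 mL partly on tolerability, and two of the three arms receive castor oil. The excluded symptoms are of the same kind as the events that the trial sets out to count.

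**Working it through.** The protocol gives no adverse event rates, no baseline symptom prevalence and no safety power, so there is no figure of its own to reproduce. The rates and values of q below are assumptions.

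**Which events are affected.** Nausea, vomiting, bloating and abdominal pain are symptoms and fall under the rule. Electrolytes are compared before and after preparation (section 2.3.7.4) and do not.

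**Formula for one symptom.** Let q be the proportion with the symptom before preparation, expected to be equal across arms by randomization. Let p be the true rate of a new or worsened symptom, taken to be the same in patients with and without it at baseline. With all randomized patients in the denominator:

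- recorded rate = (1 − q) × p
- recorded difference = (1 − q) × true difference
- recorded risk ratio = true risk ratio, because (1 − q) cancels

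**Assumed true rates of 30% (a castor oil arm) and 20% (PEG alone):**

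| q | Recorded rates | Difference | Risk ratio |
|---|---|---|---|
| 0 | 30% vs 20% | 10 points | 1.5 |
| 10% | 27% vs 18% | 9 points | 1.5 |
| 30% | 21% vs 14% | 7 points | 1.5 |
| 40% | 18% vs 12% | 6 points | 1.5 |

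**Effect on power, illustration only.** Assume true rates of 35% and 20%, two-sided alpha 0.05 and 85 per arm (the 255 of section 2.3.3 split equally, 255/3). Power is Φ[(d − 1.96·s0)/s1], where d is the difference and s0 and s1 are its standard errors under the pooled and the separate rates.

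- Worsening counted: d = 0.150, s0 = 0.0685, s1 = 0.0675, power 59%.
- Written rule, q = 30%: rates 24.5% and 14%, d = 0.105, s0 = 0.0605, s1 = 0.0599, power 41%.

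**What if the effect differs in symptomatic patients?** Keep q = 30% and rates of 35% and 20% in symptom-free patients. The recorded difference is always 0.7 × 15 = 10.5 points. The true difference is 10.5 points plus 0.3 times the difference among symptomatic patients:

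- Symptomatic 60% vs 30%: 10.5 + 0.3 × 30 = 19.5 points; the record understates it.
- Symptomatic 20% vs 20%: 10.5 + 0 = 10.5 points; no distortion.
- Symptomatic 30% vs 40%: 10.5 − 0.3 × 10 = 7.5 points; the record overstates it.

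So the rates themselves are always under-counted when worsening occurs, but the direction of error in the difference is conditional.

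**Any-event rate.** The rule drops a symptom, not a patient. Someone with baseline bloating who develops new vomiting still has an event. A patient is lost from an any-event count only if every symptom that worsened was already present, so the loss is smaller than for a single symptom.

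**The case against.** A reader might infer that the rule specifically hides harm from castor oil and necessarily pushes the comparison towards no difference. The documents do not support that:

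- The rule applies to all three arms, PEG alone included, and under equal relative effects the risk ratio does not move.
- Shrinkage of the absolute difference needs all randomized patients in the denominator. The article defines no adverse event denominator; if only symptom-free patients were counted, the difference would not be diluted.
- The Introduction's statement that castor oil "may be more likely to cause some adverse effects such as abdominal cramping, vomiting, nausea, abdominal fullness, fainting, and insomnia" concerns 50 or 60 mL. For 30 mL, the trial dose, it cites a lower incidence than with sodium phosphate.
- Nothing in the article says how often these symptoms are the reason for colonoscopy, and the exclusion criteria may lower their prevalence.

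The wording can also be defended. Section 2.3.7.3 opens with a duty to record all events related to the regimen, so the last sentence may be aimed at unchanged background complaints, and the full protocol or form instructions may say so. Section 2.3.6 requires treatment given for serious side effects to be recorded. The 4-point tolerance item and the willingness question (section 2.3.7.2) may pick up part of the burden.

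These arguments limit the size and direction of the effect, and they stand. They do not remove the defect. The exclusion is an explicit rule, not a detail left out, and it contains no exception. A treatment record or an overall tolerance score does not supply a symptom-specific event with a severity grade.

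**Conclusion.** The concern holds in a limited form. As written, the rule leaves regimen-induced worsening of a pre-existing symptom unrecorded, and symptom-specific adverse event rates are under-counted in every arm. If rates are equal with and without the symptom at baseline and all randomized patients are counted, the proportional loss in each rate and in the absolute difference equals q. With other effects in symptomatic patients, the difference could be understated, unchanged or overstated.

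The prevalence q is unknown, and the baseline items listed may not allow it to be estimated afterwards. The matter is confined to a secondary safety outcome and should be corrected; it does not threaten the primary analysis.

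**What to change.** Replace the closing sentence of section 2.3.7.3 with a rule along these lines: symptoms and their severity are recorded before the first dose; any symptom that is new, or that increases in severity or frequency after the first dose, is an adverse event; only symptoms unchanged from baseline are not counted.

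The baseline grading can be done at the existing visit on the day before colonoscopy, since the first dose is not taken until that evening. Reporting risk differences with confidence intervals, with the denominator stated, would make the safety results easier to read.

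The cost is one sentence and a short extra line on the case report form. No extra visit is needed and treatment does not change. Observed adverse event rates will be higher than under the present rule, by an amount that depends on q.

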##### Laboratory tests

2.3.7.4

The 2 mL blood sample will be collected before and after the bowel preparation. These all samples will be transferred to clinical laboratory of Chongqing University Cancer Hospital & Chongqing Cancer Institute & Chongqing Cancer Hospital in order to know and further compare the change of all electrolytes such as serum sodium and potassium. All blood samples will be probably handled after analyzed in accordance with Chinese guidelines of Good Clinical Practice (GCP).

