#### Sample size calculation

2.3.3

The bowel preparation efficacy will be primarily tested, and thus we will calculate the anticipated sample size based on this given outcome. According to the findings from the previous studies,^[18,20]^ we propose that the rate of adequate bowel preparation in 3 L PEG, combination of 2 L PEG and 30 mL castor oil, and combination of 1 L PEG, 30 mL castor oil and 5 g ascorbic acid will be 85%, 90%, and 95%. We assumed the significance and power to be 0.05% and 80%, respectively, and thus the sample size required to detect difference will be 255 patients. Because the dropout rate is expected to be 10%, totally 282 patients should be enrolled.

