##### Statistical analysis

2.3.7.6

In this study, we will adopt intent-to-treat (ITT) and per-protocol (PP) method to analyze all data. Demographic and clinical characteristics will be summarized with means, medians, and standard deviations. To assess differences between groups, data will be analyzed with Mann–Whitney *U*-test, Student's *t* test and Chi-square test according to the variables evaluated. Differences between groups regarding the bowel preparation efficacy will be analyzed with the Chi-square test. We will perform the subgroup analyses according to the indication for colonoscopy and previous history of colonoscopy. It is noted that all statistical analyses will be conducted with 2-tailed test, and *P* values of < .05 will be considered as considered significant. All statistical analyses will be performed by blinded professional statisticians with SPSS ver. 17.0 for Windows (SPSS Inc., Chicago, IL).

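### Electrolyte change is compared with unadjusted two-sample tests although each patient's baseline is collected; adjusting for it is a minor, nearly free gain in precision

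*Protocol article*

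**What the plan says.** Protocol article, section 2.3.7.4 (Laboratory tests): "The 2 mL blood sample will be collected before and after the bowel preparation". The stated purpose includes to "further compare the change of all electrolytes such as serum sodium and potassium". So each patient should have one baseline and one post-preparation value, and the quantity to be compared is the change.

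Protocol article, section 2.3.7.6 (Statistical analysis): ITT and PP methods are to be applied to all data. On methods, "To assess differences between groups, data will be analyzed with Mann–Whitney" begins a list that continues with Student's t and ends "test and Chi-square test according to the variables evaluated". The section also states that "all statistical analyses will be conducted with 2-tailed test", with P below 0.05 as the threshold. The article names no model with a covariate.

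Electrolyte imbalance appears as an example of an adverse event in section 2.3.7.3. Electrolyte change is neither the primary outcome (section 2.3.7.1) nor in the list of secondary outcomes (section 2.3.7.2).

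**The concern.** A comparison of change fixes the slope of the after value on the before value at 1. ANCOVA estimates that slope from the data. If the true slope is below 1, an arm that by chance starts high will tend to show a larger fall whatever the preparation does, and the change comparison attributes that to the arm. Adjusting for baseline removes it.

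Electrolytes are a sensible place to want precision in this design. Under section 2.3.5 the two castor oil arms drink 1 L and 2 L of water where the control arm drinks PEG, so a between-arm shift in sodium or potassium is plausible. The sample size in section 2.3.3 is set on adequacy of bowel preparation alone, so nothing secures precision for the electrolytes. At stake is the width of the confidence interval for a safety measure, not the validity of the comparison.

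**Working it through.** **The plan's own figure.** The article gives no SD, correlation, detectable difference or sample size for electrolytes, so there is nothing to reproduce.

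**Inputs**
- Evaluable patients: section 2.3.3 says "the sample size required to detect difference will be 255 patients". With equal allocation, which is an assumption because no ratio is stated, that is 255/3 = 85 per arm. The total is taken as printed and only sets the scale; the variance ratios do not depend on it.
- Significance level: 0.05 two-sided, from section 2.3.7.6.
- Before–after correlation r: not in the article; assumed over 0.3 to 0.9.
- SD: before and after taken as equal at first (assumption), then relaxed.

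**Variance of the difference between two arms, n per arm, common SD s**
- Change score: 2(1−r) × s² × 2/n
- ANCOVA, large sample: (1−r²) × s² × 2/n
- Ratio, ANCOVA to change: (1−r²) / [2(1−r)] = (1+r)/2

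The minimum detectable difference at 80% power is (1.960 + 0.842) × the square root of the variance. At r = 0.5 and n = 85 this is 2.802 × √(2 × 1.00/85) = 0.43 SD for change and 2.802 × √(2 × 0.75/85) = 0.37 SD for ANCOVA.

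| r (assumed) | Variance ratio | Equivalent extra patients | Detectable difference, change / ANCOVA (SD) | Power of change test where ANCOVA has 80% |
|---|---|---|---|---|
| 0.3 | 0.65 | 1/0.65 − 1 = 54% | 0.51 / 0.41 | 62% |
| 0.5 | 0.75 | 1/0.75 − 1 = 33% | 0.43 / 0.37 | 68% |
| 0.7 | 0.85 | 1/0.85 − 1 = 18% | 0.33 / 0.31 | 73% |
| 0.9 | 0.95 | 1/0.95 − 1 = 5% | 0.192 / 0.187 | 78% |

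**Where the excess variance comes from.** 2(1−r) = (1−r²) + (1−r)². The second term is the contribution of chance baseline imbalance. At r = 0.5 this reads 1.00 = 0.75 + 0.25. In one trial with 85 per arm, a baseline difference of one standard error is √(2/85) = 0.153 SD. At r = 0.5 it moves the difference in change by (1 − 0.5) × 0.153 = 0.077 SD.

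**Unequal SDs.** With λ = SD after / SD before, the ratio is λ²(1−r²) / (1 + λ² − 2rλ). At r = 0.8 and λ = 1.25 this is 1.5625 × 0.36 / (1 + 1.5625 − 2.00) = 0.5625/0.5625 = 1.00. The slope is rλ = 1, and there is no gain.

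**Cost of estimating the slope.** The inflation is about 1/(2n−4) = 1/166 = 0.6% of variance in a two-arm comparison with 85 per arm.

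**Simulation check** (4,000 two-arm trials, 85 per arm, true difference 0.35 SD, equal SDs). The variance ratio was 0.742 against 0.75 at r = 0.5, and 0.848 against 0.85 at r = 0.7. Mean estimates for change and ANCOVA were 0.3487 and 0.3486 at r = 0.5, and 0.3475 and 0.3476 at r = 0.7. The two methods target the same effect and differ only in precision.

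These formulas describe the t test on change. The Mann–Whitney option was not quantified.

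**The case against.** The laboratory sentence mainly explains why blood is drawn twice, and the sentence on tests does not mention electrolytes. ANCOVA of change with baseline as covariate gives the same arm effect as ANCOVA of the after value and is also a comparison of change, so the laboratory wording alone is compatible with adjustment. A separate analysis plan, not shown, might provide it.

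Part of this stands: the article does not say that adjustment is ruled out, and a reader should not infer that. But it names both the quantity and the tests for between-group differences, and none of those tests is adjusted. Read as published, the plan is an unadjusted comparison of change, and a later adjustment would add to the stated methods.

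The objections about size also stand. Two stronger readings are tempting, and neither is supported:
- That the planned comparison is biased or invalid because of regression to the mean. Randomisation balances baseline in expectation, and the simulation shows the same mean effect for both methods. The imbalance is a matter of chance in a single trial.
- That adjustment always wins, and by a wide margin. The statement that change is no more precise is a large-sample one. When the slope is close to 1, the change score can be marginally better by the 0.6% spent on the slope. With a high correlation the gain is only 5%.

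**Conclusion.** The point holds as a minor efficiency gain. The published comparison is sound but does not make full use of the baseline values that the trial already collects.

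With equal SDs, adjustment would cut the variance by 35%, 25%, 15% or 5% at r = 0.3, 0.5, 0.7 or 0.9. The article does not allow a choice within that range, and the gain is nil if the slope of after on before is 1. The per-arm figures further assume equal allocation and 255 evaluable patients.

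A reader might infer that the trial's safety conclusions are in doubt. The documents do not support that: no sample size or stated decision rule rests on the mean electrolyte shift, and electrolyte imbalance is also recorded as an adverse event with severity, outcome and action taken.

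**What to change.** Add one sentence to section 2.3.7.6. Each post-preparation electrolyte value (or its change, which gives the same arm effect) is analysed by ANCOVA with arm and the patient's pre-preparation value, and adjusted between-arm differences are reported with 95% CIs. Keep mean change per arm as a description. State that a rank-based or transformed version will be used if values are clearly skewed, so that the protection offered by the Mann–Whitney option is not lost.

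The cost is that sentence and one extra model parameter, about 0.6% of variance at about 85 per arm. No further patients, samples or visits are needed, and the model is standard in the software the article names. The change should be made before the data are analysed.
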